#### Clinical outcomes

The COMET initiative was consulted to assess for a pertinent core outcome set (COS) [30]. After reviewing the database, no COS for preoperative weight loss was identified. The efficacy outcomes include those in which preoperative weight loss could have a plausible effect:Overall 30-day postoperative morbidity (primary): This will be defined as any deviation from the usual postoperative course within 30 days of the index operation and will be a composite of system-specific complications (Additional file 2) (adjudicated outcome)30-day system-specific complications (secondary) (adjudicated outcome)30-day postoperative mortality (secondary) (adjudicated outcome)Preoperative weight loss (secondary): Preoperative weight loss will be assessed by measuring the post-VLED weight on the date of surgery and adjusting for the baseline weight in kilogramsOperative time (secondary): Operative time will be measured as the time between first skin incision and closure of the last surgical wound in minutes and will be retrieved from the patient EMRsIntraoperative blood loss (secondary): This will be measured in milliliters and collected from the patient chartIntraoperative complication (secondary): This will be defined as any documented complication in the operative note from the index procedure that aligns with any one of the following: hemorrhage: more than 1000 mL of intraoperative blood loss and/or receipt of a blood transfusion[31], iatrogenic injury to nearby organ/structure, conversion to open procedurePostoperative LOS (secondary): This will be measured in days and collected from the patient chartSurgeon-perceived difficulty (secondary): Surgeon-perceived difficulty will be evaluated with a short electronic questionnaire administered immediately following completion of the case. Questionnaires for non-bariatric abdominal and orthopedic surgery are currently being created and validated by the present research team.Quality of life (secondary): This will be assessed at baseline, following completion of the VLED, and 30 days postoperatively using the Short-Form 36 (SF-36). The SF-36 has been validated in previous cohorts of patients undergoing non-bariatric surgery [32, 33].

### Follow-up schedule

Patients will be followed at baseline, following completion of their VLED prior to surgery, and 30 days following their index surgery date (Table 1).

**Table 1 Tab1:** Standard Protocol Items: Recommendations for Interventional Trials (SPIRIT) figure for participant timeline

Activity	Before randomization	− 23	After randomization			
	** − 60 to − 23**		** − 23 to − 2**	**0**	**0 to discharge**	** + 30**
Eligibility assessment	X					
Informed consent	X					
Randomization		X				
Intervention (i.e., VLED)			X			
Baseline demographic data	X					
Operative data collection				X		
Baseline anthropometrics	X					
Post-intervention anthropometrics				X		
Post-surgical anthropometrics						X
Intervention-associated adverse events			X	X	X	X
Postoperative morbidity					X	X
Surgeon perceived difficulty				X		
QoL assessment (i.e., SF-36)	X			X		X
Intervention compliance			X	X		
Follow-up completion						X

*VLED*, very low-energy diet; *QoL*, quality of life

#### Baseline

Demographic data will be collected as well as anthropometric measures. Number of patients approached, number of patients consented, and number of patients declined, as well as reasons patients declined, will be recorded to assess feasibility. QoL data will be ascertained via administration of an in-person paper SF-36 questionnaire by a blinded research assistant.

#### Post-VLED completion

Patient-reported compliance will be assessed via a patient-completed diet diary that they will complete daily during the 3-week period prior to surgery. Both the treatment and control arms will complete these forms and give them to the research assistant in an opaque envelope on the date of their surgery. Patients in the control arms will be instructed to leave the VLED component of the form blank. Anthropometric measures will take place through a blinded research assistant. VLED-related safety data will be ascertained via a combination of patient self-reporting and EMR data. Paper questionnaires will be used to assess the presence of adverse events. QoL data will be ascertained via administration of an SF-36 questionnaire. Intraoperative difficulty will be assess using a short survey immediately following completion of the operation.

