### Planned trial interventions

#### Intervention group (VLED protocol plus counseling)

All patients in the intervention group will receive patient counseling on weight loss and an active VLED protocol. The preoperative VLED protocol will utilize commercially available weight loss products, such as Optifast® 900, Medimeal®, or a similar product. Patients will receive a 3-week supply. They will start taking the VLED 3 weeks and 2 days prior to their surgery date (i.e., 23 days prior to their surgery date) and finish the intervention the evening of their second last day prior to surgery. This timeframe was chosen to not interfere with any other perioperative intervention required for a given surgery (e.g., bowel preparation, carbohydrate loading). They will be instructed to consume four packets daily. This provides a total energy intake of 900 kcal. Patients will also be able to consume up to 2 cups of low-calorie vegetables per day along with the meal replacement product. They will be provided with a handout containing specific instructions. Patients will keep self-report diaries of their dietary intake and activity levels. Patients enrolled in the trial and assigned to the VLED group who are diabetics will be referred to a diabetes educator nurse practitioner for management of their insulin dosing and/or other anti-hyperglycemic medications throughout the duration of the intervention period.

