#### Control group (counseling alone)

The control group patients will receive the pre-existing standard of preoperative care, which may include counseling for weight loss without prescription of a specific preoperative weight loss intervention, as this is meant to be a pragmatic trial. Currently, there are no standardized interventions aimed at optimizing obese patients prior to undergoing non-bariatric surgery. Briefly, counseling may consist of the surgeon, at the time of the preoperative clinic visit, discussing weight loss strategies such as decreased caloric intake and increased physical activity. Patients will not receive prescriptions for preoperative VLEDs, any other weight loss supplement, or any physical activity intervention aimed at promoting weight loss prior to surgery. Patients will keep self-report diaries of their dietary intake and activity levels.

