#### Feasibility outcomes

Randomization percentage: Defined as the number of patients agreeing to participate in the RCT and being randomized to treatment or control divided by the number of patients approached for participation in the RCT. A randomization percentage of 70% or greater will support the feasibility of a full RCT. A lesser randomization percentage may be feasible with modifications.Recruitment rate: Defined as the number of patients randomized into the RCT per month. We will aim for a rate of 16 patients per month (i.e., 4 patients at each of 4 sites per month). A recruitment rate of equal to or greater than this will support the feasibility of a full RCT. A lesser recruitment rate may be feasible with additional sites for the full RCT. At present, we anticipate participation of at least 10 sites in the definitive trial. If each site recruited at least 4 patients per month, this would equate to a minimum 48 patients per year at a given site. Thus, recruitment over 2.5 years would achieve our anticipated study sample size of approximately 1200.Intervention adherence: Defined as the number of preoperative VLED doses taken divided by the total number of doses prescribed for each participant randomized to the intervention arm. Adherence will be self-reported via written diaries. A mean adherence of greater than 80% (i.e., completing 80% or more of doses) will be our benchmark for feasibility in the present study. Adherence will also be measured through matching actual preoperative weight loss with expected preoperative weight loss. As per our systematic review evaluating preoperative VLEDs in patients undergoing bariatric surgery, patients receiving preoperative VLEDs for 2–3 weeks prior to bariatric surgery, they loss approximately 5% of their pre-VLED weight [18]. Therefore, a study participants expected weight loss will be defined as 5% of their pre-VLED in kilograms. We will subtract their expected weight loss from their actual weight loss as a measure of adherence.Follow-up completion: Defined as completion of the pre-VLED, post-VLED, and 30-day postoperative visits, along with complete anthropometric measures and study questionnaires. A follow-up completion rate of greater than 90% will support the feasibility of a full RCT.Network development: Defined as recruiting from all four participating centers at the aforementioned rate. Additionally, we will aim to extend our multi-disciplinary network to at least 10 centers throughout the course of this pilot RCT in preparation for the full RCT.Other findings: Unexpected and/or findings unique to this pilot trial will be reported narratively.

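### Telling controls to leave the diary's VLED section blank removes the pilot's only structured record of control-arm VLED use

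*Protocol article*

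**What the plan says.** Under Post-VLED completion, the protocol article describes a diary filled in daily over the three weeks before surgery: "Both the treatment and control arms will complete these forms and give them to the research assistant in an opaque envelope". It then adds: "Patients in the control arms will be instructed to leave the VLED component of the form blank".

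Four other places bear on this:

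- **Intervention group:** "The preoperative VLED protocol will utilize commercially available weight loss products, such as Optifast® 900, Medimeal®, or a similar product".
- **Control group:** "Patients will not receive prescriptions for preoperative VLEDs, any other weight loss supplement, or any physical activity intervention". Buying a product oneself is not addressed. The same section also says: "Patients will keep self-report diaries of their dietary intake and activity levels".
- **Feasibility outcomes:** dose adherence is "Defined as the number of preoperative VLED doses taken divided by the total number of doses prescribed for each participant randomized to the intervention arm". None of the listed feasibility outcomes concerns VLED use among controls.
- **Clinical outcomes:** "Preoperative weight loss will be assessed by measuring the post-VLED weight on the date of surgery". This is not restricted to one arm, and Table 1 schedules anthropometrics at baseline and on the day of surgery.

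Trial design names the surgeon, outcome assessor and data analyst as blinded. Patients are not named.

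**The concern.** Control patients know their allocation, have consented to a trial of a preoperative weight-loss diet, and may be counselled by their surgeon to lose weight. Some could start a meal-replacement diet on their own. That they can obtain the product themselves is an inference from its being commercially available; the article does not say so directly.

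The shared diary has a section made for VLED use, and controls are told not to use it. An empty section then carries no information, because it looks the same whether nothing was taken or something was taken and not written down. No later analysis can recover data that the form told patients not to enter.

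At stake is the planning of the definitive trial. The Discussion says the pilot is meant to inform the full RCT, and the Analysis strategy uses pilot morbidity data to check the full trial's power calculation. Use of the intervention by controls shrinks the contrast on which that calculation depends, and a pilot is the natural place to learn how common it is.

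**Working it through.** **1. What would record control-arm VLED use if the article is followed as written**

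| Source | Collected in controls? | Specific to VLED use? | Assigned to contamination? |
|---|---|---|---|
| VLED section of diary | No, blank by instruction | Yes | No |
| General dietary entries | Yes | Unknown, form not shown | No |
| Weight, baseline to surgery | Yes | No; counselling may cover eating less and moving more | No |
| Dose adherence | No, intervention arm only | Yes | No |

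The one source that is both direct and structured is the one left empty.

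**2. The plan's own figures**

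The article gives no contamination rate. The one precision figure it shows (Sample size calculation) is 82–95% for 90% follow-up completion in 88 patients. A Wilson interval at p = 0.90, n = 88 gives 82.0% to 94.7%, so it reproduces, and this point does not affect it. The 1158 cannot be reproduced, because its inputs are in Additional file 4, which is not shown.

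**3. What the pilot could learn if use were recorded**

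Controls: 88 patients allocated 1:1, so 88 / 2 = about 44. Exact (Clopper–Pearson) 95% intervals:

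| Users among 44 | 95% CI |
|---|---|
| 0 | 0 to 8.0% |
| 2 | 0.6 to 15.5% |
| 4 | 2.5 to 21.7% |
| 9 | 9.8 to 35.3% |

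The chance of seeing at least one user is 1 − (1 − c)^44, where c is the true share. At c = 5% this is 1 − 0.95^44 = 0.90; at c = 10% it is 1 − 0.90^44 = 0.99.

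**4. What contamination could cost the definitive trial**

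c is an assumption. If a share c of controls gets the full VLED effect, the control event rate moves from p_C to (1 − c)p_C + c·p_T. The difference between arms becomes (1 − c)(p_C − p_T). Required size varies roughly as one over the squared difference, so N(c) = 1158 / (1 − c)².

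- c = 5%: 1158 / 0.9025 = about 1284
- c = 10%: 1158 / 0.81 = about 1430
- c = 20%: 1158 / 0.64 = about 1810

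Equivalently, if 1158 is kept and its power is 80% at two-sided 5% (both assumed, since they are not shown), power is Φ[(1.960 + 0.842)(1 − c) − 1.960]. That is about 76%, 71% and 61% at c = 5%, 10% and 20%.

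A clean pilot would set a useful bound. With 0 of 44, the upper limit of 8.04% gives 1158 / (0.9196)² = about 1370 under the same assumptions.

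**The case against.** A reader might infer that contamination would be invisible in this pilot, or that the pilot would report zero VLED use in controls whatever happened. The article supports neither. Controls keep dietary diaries, so someone living on meal-replacement packets may well write that down. They are also weighed, and a control who lost close to the 5% expected under a VLED would stand out. Unexpected findings are to be reported narratively. A blank ordered by instruction is not a zero, and no planned result would report a control-arm zero. This part of the objection stands.

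The diary form is not shown. If its VLED section is a tally of prescribed packets, leaving it blank for patients prescribed none is ordinary form design, and other products would go under dietary intake. That is possible, but a control told to leave the VLED section empty could also take it to mean that such use need not be recorded. The article does not settle which.

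The sample-size figures rest on an assumed c and on full effect in every contaminated control, and Additional file 4 may already allow for crossover. The trial is described as pragmatic, so some self-directed dieting belongs to the comparator. This limits the size of the claim. It does not remove the value of knowing how many controls used the intervention itself.

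Finally, 44 controls give a wide interval: 4 of 44 covers both 10% and 20%. A daily question may also remind controls that such products exist. The first is true, yet a rough estimate is better than none. The second is probably small, because consent has already told patients about the diet, and one question at the end of the period would reduce it further.

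**Conclusion.** The point holds as a measurement weakness. The instruction removes the direct, structured measure of control-arm VLED use, leaves only general diet entries and non-specific weight change, and no listed feasibility outcome fills the gap. The definitive trial would therefore be planned without a usable contamination estimate.

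No figure, criterion or estimate in the article becomes wrong because of it, and the pilot is descriptive with no hypothesis testing. It is a cheap improvement and falls short of an essential correction.

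The increase from 1158 to about 1430 (c = 10%) or 1810 (c = 20%) is an upper-end illustration. It assumes the stated c, full VLED effect in contaminated controls, and no existing allowance in Additional file 4. Confidence is high on what the instruction says and what it removes. It is lower on how much the dietary entries would recover, because the form is not shown.

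**What to change.** Replace the instruction to leave the section blank. Have control patients record any VLED or meal-replacement product used, with product and quantity, and enter zero or none otherwise. This can be done daily on the existing form or through a single item at the end of the three weeks. Either way it is returned in the same opaque envelope, so the research assistant's blinding is no worse than now; a blank section would reveal allocation as readily as zeros.

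Report the proportion of controls with any use, with its 95% CI, as a descriptive feasibility result beside intervention-arm adherence.

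The cost is one protocol sentence, one diary instruction and one reported proportion, with no new visit or staff. The downside is a small reminder effect in controls, which the end-of-period item lessens at the price of poorer recall. Any change has to be in place before diaries are issued, because use that was not recorded cannot be reliably recovered later.

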#### Thirty days postoperatively

Postoperative outcomes will be ascertained via review of the EMR. They will be reviewed on the date of surgery and at 30 days postoperatively. We will assess operative time, intraoperative blood loss, and postoperative LOS via EMRs. Anthropometric data will be measured. QoL data will be ascertained via administration of an SF-36 questionnaire. The number of patients completing the 30-day postoperative follow-up will be recorded to assess feasibility.

### Sample size calculation

We propose a pilot RCT of 88 patients (i.e., 22 patients per site) to assess the feasibility of a full RCT aimed at determining the efficacy of preoperative VLED at improving short-term postoperative outcomes in obese patients undergoing non-bariatric surgery. This sample size is sufficient to ascertain our feasibility objectives and is approximately 7.5% of the size of a definitive trial. A full RCT would require 1158 patients (Additional file 4). We justified our proposed sample size of 88 patients based on 95% CIs for one of our feasibility outcomes. Specifically, to assess for 90% follow-up completion, 88 patients would provide 95% CIs of 82–95%, which we believe is adequate precision.

The anticipated recruitment rate is 16 patients/month. Given that patient enrollment will continue to 88, we anticipate recruitment will be complete within 6 months. A review of the 2018–2019 St. Joseph’s Healthcare Hamilton database including patients undergoing non-bariatric abdominal surgery, plastic surgery, otolaryngology surgery, and orthopedic surgery suggests 300–400 elective non-bariatric surgeries/month. A review of local retrospective studies suggests that 40–50% of patients undergoing non-bariatric surgery are obese (i.e., BMI > 30 kg/m^2^). Therefore, there will be approximately 120–160 potentially eligible patients per month. Across four sites, this equates to approximately 480–640 patients/month that may be eligible [34, 35]. Thus, a total recruitment of 16 patients/month is a plausible estimate across four sites.

### Analysis strategy

Descriptive statistics will be used to characterize the study sample. The outcomes of the pilot study will be descriptive in nature and will focus on feasibility. Differences in binary outcomes will be presented using absolute differences and corresponding 95% CIs. Similarly, differences in continuous outcomes will be presented as mean differences with 95% CIs. We will not conduct hypothesis testing for outcomes [36]. We will calculate aggregated measures for 30-day postoperative morbidity to compare this to the power calculation for the full RCT, to ensure an accurate power calculation is performed for the full RCT. There will not be a planned interim analysis in the present study. There are no subgroup analyses planned [37].

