### Study centers

This pilot trial will include 4 centers: (1) St. Joseph’s Healthcare Hamilton (local); (2) Juravinski Hospital, Hamilton (local); (3) Hamilton General Hospital (local); (4) Kingston Health Sciences (outside site). Throughout the pilot RCT, we will be seeking active engagement from at least 6 other centers to have at least 10 centers involved in the full RCT.

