### Recruitment

Patient recruitment will occur at Hamilton Health Sciences (i.e., Juravinski Hospital, Hamilton and Hamilton General Hospital), St. Joseph’s Healthcare Hamilton, and Kingston Health Sciences. All surgeons who perform elective non-bariatric surgery at these sites will be made aware of the study via workshops and internal communications. Patients will be identified by the surgeons, their administrative assistants, patient navigators, and/or study investigators at the time of referral or at the time of their initial preoperative consultation. Surgeons and/or other clinicians within a patient’s circle of care will introduce the study to participants at the time of their preoperative visits. Patients meeting inclusion criteria based on a review of their electronic medical record will be approached by designated research personnel at the time of their initial surgical consultation in clinic. If the patient is not identified in time, or if it is not feasible for the research personnel to approach the patient in person at the time of their consultation, the patient will be contacted by telephone within one-week of their consultation. At the time of initial contact between the study personnel and patient, the study will be introduced, and eligibility will be confirmed. Once eligibility is confirmed, the written informed consent process will ensue. After documentation of written informed consent, patients will be registered using a web-based randomization system. Consecutive patients will be allocated 1:1 according to a computer-generated randomization schedule to one of the two treatment arms. Randomization will be stratified by center and will employ randomly permutated blocks.

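### The planned between-arm differences name neither baseline SF-36 nor the randomization center; using both would tighten the SF-36 interval at no data cost (minor improvement)

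*Protocol article*

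**What the plan says.** All of this is in the protocol article.

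- **Analysis strategy.** For binary outcomes, "Differences in binary outcomes will be presented using absolute differences and corresponding 95% CIs". For continuous outcomes, "differences in continuous outcomes will be presented as mean differences with 95% CIs". No covariate and no stratification is named. The same section states "The outcomes of the pilot study will be descriptive in nature and will focus on feasibility" and "We will not conduct hypothesis testing for outcomes".
- **Recruitment.** "Consecutive patients will be allocated 1:1 according to a computer-generated randomization schedule", and "Randomization will be stratified by center and will employ randomly permutated blocks". Under Study centers there are four sites: three local hospitals and one outside site.
- **Clinical outcomes.** For SF-36: "This will be assessed at baseline, following completion of the VLED, and 30 days postoperatively using the Short-Form 36 (SF-36". No baseline adjustment is given for it. For preoperative weight loss, the same section does say that the day-of-surgery weight is adjusted for baseline weight.
- **Sample size calculation.** The total is 88 (22 per site), justified by a 95% CI of 82–95% around 90% follow-up completion.

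**The concern.** Two pieces of information are fixed before treatment starts and are available for every between-arm comparison of SF-36: the patient's own baseline score and the center within which allocation was balanced. The analysis text uses neither. The article does reach the level of detail at which adjustment is mentioned, since it states it for weight. A statistician who follows the text literally would therefore adjust weight and compare SF-36 as a plain two-group difference, with no reason given for treating the two differently.

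What is at stake is precision. With no hypothesis tests, estimates and intervals are the form in which the between-arm clinical results will appear. Leaving out a correlated baseline makes the SF-36 interval wider than it need be. Leaving out a prognostic stratification factor makes an interval mildly conservative. Settling the model in advance also removes a later choice between an adjusted and an unadjusted SF-36 result.

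**Working it through.** **Inputs.** From the article: N = 88, four centers of 22, 1:1 allocation, hence about 44 per arm and 11 per arm per center. Assumed, because the article gives no values: the correlation r between baseline and follow-up SF-36, the share R² of outcome variance explained by center, and center-specific event rates.

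**1. The plan's own figure.** Wilson interval for p = 0.90, n = 88, z = 1.96:
- midpoint = (0.90 + 1.96²/176) / (1 + 1.96²/88) = 0.8833
- half-width = 1.96 × √(0.09/88 + 1.96²/(4 × 88²)) / (1 + 1.96²/88) = 0.0636
- result: 82.0% to 94.7%, which rounds to the stated 82–95%.

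This is a one-sample proportion. It reproduces, and no between-arm adjustment changes it.

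**2. SF-36, unadjusted.** Half-width in SD units = t(0.975; 86 df) × √(2/44) = 1.988 × 0.2132 = 0.424.

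**3. SF-36, adjusted for baseline (ANCOVA).** Half-width = t(0.975; 85 df) × √[(2/44)(1 − r²)(1 + 1/83)], where the last factor is the small-sample penalty for estimating the slope.

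| Assumed r | Half-width (SD) | Ratio to unadjusted | Change in width |
|---|---|---|---|
| 0 | 0.426 | 1.006 | 0.6% wider |
| 0.3 | 0.407 | 0.960 | 4% narrower |
| 0.5 | 0.369 | 0.871 | 13% narrower |
| 0.6 | 0.341 | 0.805 | 20% narrower |
| 0.7 | 0.305 | 0.719 | 28% narrower |

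Ignoring the small-sample penalty, the gain at r = 0.6 is worth 1/(1 − 0.36) = 1.56 times the sample, or about 56% more patients for this outcome. If only 79 patients (about 90% of 88) have complete data, the ratios barely move: 0.961, 0.872, 0.806 and 0.719 for r = 0.3, 0.5, 0.6 and 0.7.

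**4. Center, continuous outcomes.** Three center terms leave 83 df. Ratio = [t(0.975; 83 df)/t(0.975; 86 df)] × √(1 − R²).
- R² = 0: 1.0005 (0.05% wider)
- R² = 0.01: 0.9955 (0.5% narrower)
- R² = 0.05: 0.975 (2.5% narrower)
- R² = 0.10: 0.949 (5.1% narrower)

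At R² = 0.10 an interval that ignores center is too long by a factor 1/√0.9 = 1.054. Its critical value is in effect 1.988 × 1.054 = 2.10, so its coverage is about 96% and not 95%.

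**5. Center, binary outcomes.** Simulation of 20,000 trials per row, 11 per arm per center, same rates in both arms. Crude risk-difference interval against a center-stratified one, with within-center variances on the n − 1 divisor.

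| Assumed center rates | Crude width | Stratified width | Change |
|---|---|---|---|
| 20% in all four | 0.329 | 0.333 | about 1% wider |
| 15, 20, 20, 25% | 0.329 | 0.332 | 0.7% wider |
| 10, 15, 25, 30% | 0.330 | 0.327 | 0.9% narrower |
| 5, 15, 25, 35% | 0.330 | 0.320 | 3% narrower |
| 10, 20, 40, 50% | 0.379 | 0.359 | 5% narrower |

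**The case against.** The strongest objection is that the text names effect measures, not models. A mean difference can come from ANCOVA and a risk difference can be stratified. A reader might infer that the plan commits to raw, unadjusted differences throughout. The documents do not support that: neither word appears, and covariates are often left to a full protocol or analysis plan, which is not shown here. What answers it in part is the article's own choice to state baseline adjustment for weight and not for SF-36.

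A reader might also infer that all the reported intervals are materially too wide. That fails too. Weight is already adjusted. Operative time, blood loss and length of stay have no baseline value, so only center could help them, and by little. The primary clinical outcome, 30-day morbidity, is binary, where center brings almost nothing.

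A third tempting reading is that the pilot's decisions suffer. They do not. The feasibility criteria are not between-arm differences. What the Analysis strategy names as input to the full trial's power calculation is aggregated 30-day morbidity, not an SF-36 contrast.

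Finally, an unadjusted comparison is unbiased under randomization and its interval already allows for chance baseline imbalance, so it is legitimate in a descriptive pilot. All of this stands and limits the point. It does not remove a gain for SF-36 that needs no new data.

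**Conclusion.** The point holds in a narrow form. The stated analysis does not name baseline SF-36 or the stratification center, and using them would be better. For SF-36, a secondary outcome, the interval would be 4% to 28% narrower for an assumed correlation between 0.3 and 0.7, with a loss of only 0.6% if the correlation were zero. For center, the reason is mainly agreement with the randomization. The gain in precision is about 0–5% for continuous outcomes if centers explain up to 10% of the variance, and negligible or slightly negative for binary ones. The correlation, the center variance and the center rates are all assumptions. This is a minor, free improvement. It does not show that any planned interval is invalid, and it leaves the feasibility outcomes, their thresholds and the 82–95% interval behind N = 88 untouched.

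**What to change.** In the Analysis strategy, replace the statement on continuous outcomes with wording such as: *Differences in continuous outcomes will be estimated from a linear model with arm and center, plus the baseline value where one is collected (SF-36 at each follow-up time, and weight), and reported with 95% CIs. Unadjusted summaries by arm will also be tabulated.*

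For binary outcomes, a center-stratified (Mantel-Haenszel) risk difference is optional, for consistency with the design and not for precision. If it is used, the variance needs care with 11 patients per arm per center. In the simulation with equal rates of 20%, a plain binomial variance within centers made the interval about 4% narrower than the crude one, when the true sampling spread called for a slightly wider one.

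The cost is one sentence and about four degrees of freedom (three for center, one for baseline). No new data are needed. If an analysis plan already contains this model, a reference to it would be enough.
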